## Abstract

**Background::**

Chronic kidney disease (CKD) is a progressive and irreversible loss of kidney function. After stage 3, there will be increased risks of hypertension, heart failure, bone disease, anemia, gastrointestinal symptoms, and progression to end-stage kidney failure without proper intervention and treatment. Compound α-ketoacid tablets (KA) administration plays an important role in clinical CKD adjunctive therapy for patients with restricted protein intake. Bailing Capsule (BC), a commonly used Chinese patent medicine for renal diseases, could regulate human immune function, repair renal tubular epithelial cells, prevent renal tubular atrophy, and reduce kidney damage to improve renal function. In this study, we try to conduct a double-blinded, randomized, controlled trial to observe the efficacy and safety of BC combined with KA in treating patients with stage 3 CKD.

**Methods::**

This is a double-blinded, randomized, controlled trial. Patients will be randomly divided into treatment group (BC and KT) and control group (BC-simulation and KT) in a 1:1 ratio according to random number table. The treatment course will be 8 weeks, and the changes of subjective symptoms, patient global assessment (PGA) scale, serum creatinine, cystatin C, and estimated glomerular filtration rate, all related adverse events, vital sign measurements, and physical examinations will be recorded. SPSS 21.0 will be used for data analysis.

**Conclusions::**

The results will show whether BC combined with KA could alleviate the symptoms of fatigue, anorexia, halitosis, nausea, itching, and edema, improve kidney function in patients with CKD at stage 3.

**Trial registration::**

OSF Registration number: DOI 10.17605/OSF.IO/24AJ7.

## Introduction

1

Chronic kidney disease (CKD) is a progressive and irreversible loss of kidney function, with an increased prevalence in recent years.^[1,2]^ It is mainly caused by diabetes, hypertension, and glomerulonephritis.^[3,4]^ Initially, the symptoms of CKD are insidious and then presented with fatigue, swelling legs, dizziness, and loss of appetite gradually. After stage 3, the above symptoms become more obvious, with increased risks of hypertension, heart failure, bone disease, anemia, gastrointestinal symptoms, and a progress to end-stage kidney failure without proper intervention and treatment.^[5,6]^

At present, the main principles for CKD are treating original diseases, low-protein diet, essential amino acids intake, and management of complications. Although it could slow down the damage to kidney function, long-term low-protein diet can aggravate malnutrition in patients. Compound α-ketoacid tablets (KA) administration plays an important role in clinical CKD adjunctive therapy for patients with restricted protein intake.^[7,8]^ With appropriate proportioned essential amino acids, KA could promptly meet the needs of human synthesis to improve the protein metabolism disorder. In addition, KA could reduce insulin resistance and increase esterase activity, thereby improving patients’ glucose and lipid metabolism.

In China, Bailing Capsule (BC) is a commonly used Chinese patent medicine for renal diseases.^[9,10]^ It is composed of Cordyceps mycelium, which is rich in a variety of trace elements, amino acids, adenosine, and cordycepin to improve blood circulation, inhibit neurotransmitter release and regulate adenylate cyclase activity. Studies have shown that BC could regulate human immune function,^[11–13]^ repair renal tubular epithelial cells, prevent renal tubular atrophy, and reduce kidney damage to improve renal function.^[14,15]^ Our group tried to use the combination of BC and KA to treat CKD patients, and we preliminarily found the therapy could improve the symptoms of fatigue and dizziness to improve the quality of life. However, there are few highquality studies to observe the efficacy of BCs and α-ketoacid tablets in the treatment of stage 3 CKD. In this study, we try to conduct a double-blinded, randomized controlled trial to observe the efficacy and safety of BC combined with KA in treating patients with stage 3 CKD.

## Methods

2

### Study design

2.1

From June 1st, 2021 to May 31st, 2022, the double-blinded, randomized controlled trial with a registration number of DOI 10.17605/OSF.IO/24AJ7 will be conducted in the First Hospital of Hebei Medical University. The trial has been approved by the Health Research Ethics Board in the hospital. The procedure will be in accordance with the Declaration of Helsinki. The study design is shown is Figure 1.

**Figure 1 F1:**
[figure not shown]
Flow diagram of the study.

### Patients

2.2

CKD patients referring to the First Hospital of Hebei Medical University will be assessed for screening. Before randomization, a written informed consent will be signed for all the patients or or authorized persons, and they are free to discontinue the trial at any time.

The inclusion criteria are as follows:

1.aged 18 to 80 years’ old;2.CKD in stage 3 (30 mL/min/1.73 m^2^<estimated glomerular filtration rate<59 mL/min/1.73 m^2^);3.with written informed consent.

The exclusion criteria are as follows:

1.with a history of allergic to ingredients of BC or KA;2.with a history of kidney transplant;3.with uncontrolled diabetes (HbAlc) >10% and hypertension (systolic blood presuure ≥170 mmHg or diastolic blood pressure ≥100 mmHg);4.complicated with hepatic impairment, infection, or malignant tumor;5.women in pregnant or lactating.

### Randomization and blinding

2.3

Patients will be randomly divided into treatment group (BC and KT) and control group (BC-simulation and KT) in a 1:1 ratio according to random number table. The physician, patients, assessors, and analysts will all be blinded to the allocation. The BC-simulation is presented in the same package, appearance, and taste with BC to maintain blinding.

### Interventions

2.4

The same initial treatment will be applied to patients in both groups with medicines to protect the kidney, reducing blood pressure, regulating lipid. Patients will also be educated to take high-quality low-protein diet and regular exercise and rest.

In the treatment group, patients will take 2 g BCs (Hangzhou Zhongmei Huadong Pharmaceutical Co. Ltd, Z10910036) 3 times daily and 2.52 g Compound α-ketoacid tablets (Beijing Fresenius Kabi Pharmaceutical Co., Ltd, H20041442) 3 times daily simultaneously for 8 weeks.

In the control group, patients will take 2 g BC-simulations (Hangzhou Zhongmei Huadong Pharmaceutical Co. Ltd) 3 times daily and 2.52 g Compound α-ketoacid tablets (Beijing Fresenius Kabi Pharmaceutical Co., Ltd, H20041442) 3 times daily simultaneously for 8 weeks.

### Outcome measures

2.5

The primary outcomes are the changes of subjective symptoms of fatigue, anorexia, halitosis, nausea, itching, and edema evaluated at week 0, week 4, and week 8. The corresponding score will be 2, 4, and 6, respectively, according to the degree of mild, moderate, and severe. The secondary outcomes are patient global assessment scale, serum creatinine, cystatin C, and estimated glomerular filtration rate at week 0 and 8. The patients will be followed for another 4 weeks after the treatment. The incidence and types of related adverse events, vital sign measurements, and physical examinations will also be recorded.

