### Sample size

2.6

In our preliminary study, the change of subjective symptoms in the treatment group was 7.21 ± 4.36 and 4.35 ± 3.15 in the control group. Taking α as 0.05, β as 0.2 with a 2-sided test, and considering a dropout of 20%, 72 patients will be needed totally.

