### Statistical methods

2.7

SPSS 21.0 (SPSS Inc, Chicago, IL) will be used for data analysis. The measurement data will be expressed as mean ± standard deviation. Considering the normality and homogeneity, *t* test, or nonparametric test will be applied for the changes between the 2 groups. Repeated measurement analysis of variance or generalized linear model will be applied for repeated measurement data. *P* < .05 will be considered statistically significant.

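### The primary outcome is written as six symptoms at two post-baseline visits, but the 72 patients are sized for one summed change at an unnamed visit; 5% error and 80% power are established only for the latter.

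*Protocol article*

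**What the plan says.** Section 2.5 (Outcome measures) puts the primary outcomes in the plural: "The primary outcomes are the changes of subjective symptoms of fatigue, anorexia, halitosis, nausea, itching, and edema evaluated at week 0, week 4"; the last assessment is at week 8. On scoring it says: "The corresponding score will be 2, 4, and 6, respectively, according to the degree of mild, moderate, and severe". It does not say that the six scores are added, what an absent symptom scores, or which visit decides the trial.

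Section 2.6 (Sample size) rests on a single quantity: "the change of subjective symptoms in the treatment group was 7.21 ± 4.36 and 4.35 ± 3.15 in the control group". The visit is not given. The design values are: "Taking α as 0.05, β as 0.2 with a 2-sided test", and the result is: "considering a dropout of 20%, 72 patients will be needed totally".

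Section 2.7 (Statistical methods) offers a t test or a nonparametric test for between-group changes, and repeated-measures ANOVA or a generalized linear model for repeated data. One rule covers all of them: P < .05 "will be considered statistically significant". None of these methods is tied to a particular primary comparison.

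**The concern.** Sections 2.5 and 2.6 do not describe the same endpoint. The first lists six separately scored symptoms at two post-baseline visits, up to 6 × 2 = 12 between-group comparisons. The second uses one number that cannot belong to a single symptom.

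Without a defined total and a named visit, several different results could each be reported as meeting the primary outcome: one symptom at one visit, the total at week 4, or the total at week 8. The stated error rate and power belong to only one kind of result, a single test of a summed change. The article's planned conclusions name all six symptoms, so a reader needs to know which result the design can support.

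This is not detail that an article leaves to an analysis plan. The article does state a primary outcome, and that statement conflicts with its own sample-size basis.

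**Working it through.** **Inputs.** Section 2.6: mean changes 7.21 (SD 4.36) and 4.35 (SD 3.15), two-sided α = 0.05, β = 0.2, dropout 20%, N = 72. Section 2.3: allocation "in a 1:1 ratio according to random number table", so 36 per arm and 36 × 0.8 = 28.8 completers per arm. Section 2.5: six symptoms, top score 6 each, two post-baseline visits.

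**1. Reproducing the 72.**
- Difference = 7.21 − 4.35 = 2.86.
- Pooled SD = √((4.36² + 3.15²)/2) = 3.803.
- Standardised difference d = 2.86/3.803 = 0.752.
- Normal approximation: n = 2 × (3.803 × (1.960 + 0.842)/2.86)² = 27.8, so 28 per arm; 28/0.8 = 35 per arm, 70 in total.
- t test: 28.75, so 29 per arm; 58/0.8 = 72.5 in total, or 74 if each arm is rounded up.
- Power of the t test with 28.8 per arm: 80.1%.

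The stated 72 is therefore sound for one test of one quantity with these pilot figures.

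**2. What that quantity is.** One symptom scores at most 6, so its change cannot exceed 6. A mean change of 7.21 must combine symptoms. The sized endpoint is a summed score.

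**3. Error rate under the readings that the text leaves open, each test at .05.** Correlations are assumptions, because the article gives none.

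| Reading | Independent tests | With assumed correlation |
|---|---|---|
| Summed score, one visit, one test | 5% | 5% |
| Summed score, tested separately at both visits | 1 − 0.95² = 9.8% | about 8-9% (visit correlation 0.5-0.8) |
| Six symptoms at one visit | 1 − 0.95⁶ = 26.5% | about 16-24% (symptom correlation 0.3-0.7) |
| Six symptoms at both visits | 1 − 0.95¹² = 46.0% | about 26-40% (symptom 0.3-0.7, visit 0.5-0.7) |

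The correlated figures come from simulating equicorrelated normal test statistics.

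**4. Power for one named symptom.** This cannot be derived from the article. As an illustration, assume that the 2.86 is split evenly over six symptoms with equal SDs and common correlation r. Each symptom then has difference 2.86/6 = 0.477 and SD 3.803/√(6 + 30r), so d per symptom = 0.752 × √(6 + 30r)/6. With 28.8 per arm at two-sided .05:

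| r | d per symptom | Power |
|---|---|---|
| 0 | 0.307 | 21% |
| 0.3 | 0.485 | 44% |
| 0.5 | 0.574 | 57% |
| 0.7 | 0.651 | 68% |

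Power stays below 80% over this range.

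**The case against.** The strongest reply is that section 2.6 speaks of the change in symptoms in almost the terms of section 2.5, so the six symptoms are naturally read as components of one score. On that reading, at one visit with one test, the 5% holds, power is about 80% and 72 is right. Section 2.7 never says that each symptom is tested separately at each visit, and its repeated-measures option could give one test across visits. Twelve tests is the worst case, not a stated plan.

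Most of this stands. A reader might infer that the trial will run 12 tests at .05 and that both the 5% and the 80% therefore fail. The documents do not support that inference: they leave the number of tests open.

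Nor would inflated error and lost power necessarily occur together. If a win on any one symptom counted as success, the chance of at least one significant symptom at one visit, under the even-split assumption, would be about 1 − (1 − 0.208)⁶ = 75% at correlation 0 and roughly 90% at correlation 0.3 to 0.5 by simulation. The low per-symptom figures apply to a claim about one named symptom.

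What the reply does not remove is the gap in the text. The summed score has to be deduced from a pilot mean that is too large for one item, and the visit cannot be deduced at all. Even the favourable reading gives about 8-10% error if the sum is tested separately at weeks 4 and 8.

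**Conclusion.** The concern holds as a conflict between the declared primary outcomes and the sized endpoint. The 5% and the 80% are secured only for one summed change at one visit in one test. For the symptoms and visits as declared, neither is established. That is weaker than saying that they fail, and the weaker statement is the one that the text supports.

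The size of the problem depends on what the sponsor intends. It is nil for the summed score at one visit, about 8-10% error for the sum tested separately at both visits, and up to 26.5% or 46.0% for 6 or 12 independent tests, lower with correlation. The correlations, the equal SDs and the even split of the effect are assumptions. The non-zero correlations used give up the independence bound but do not change the order of the readings. The sample size itself is not in error. The point should be settled before unblinding, because it decides what counts as success.

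**What to change.** In sections 2.5 and 2.6:
- Define the six-symptom total score, including the score for an absent symptom.
- Declare its change from week 0 to one named visit as the single primary endpoint, decided by one test at two-sided .05. Week 8, the end of treatment, is the natural choice, provided the pilot figures refer to that visit. Section 2.6 should say which visit they come from.
- Make week 4 and the six single symptoms supportive, or test them with Holm only after the primary endpoint succeeds.

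This costs wording only. N = 72 stands, and no further data are needed. The downside is that single-symptom and week-4 results no longer count as primary evidence. If the sponsor instead wants the six symptoms as separate primaries, multiplicity must be controlled and the trial re-sized. As an illustration, Bonferroni over six tests, with d = 0.752 assumed for every symptom and 80% power for each, needs 108 patients (114 by t test) with 20% dropout.

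### Adverse-event recording is restricted to related events, so a causality judgement decides which events enter the data and the safety comparison loses sensitivity

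*Protocol article*

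**What the plan says.** The Introduction sets out to "observe the efficacy and safety of BC combined with KA in treating patients with stage 3 CKD", so safety is an aim alongside efficacy.

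The article describes adverse-event recording in two places, and both carry the same qualifier:

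- Section 2.5 (Outcome measures): "The incidence and types of related adverse events, vital sign measurements, and physical examinations will also be recorded".
- Abstract, Methods: "all related adverse events, vital sign measurements, and physical examinations will be recorded".

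Nowhere does the article say that adverse events are recorded whatever their cause. It also does not say who judges relatedness, by what criteria, or to which product the event must be related. Both arms take compound α-ketoacid tablets and background medicines (section 2.4).

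Two other statements bear on the point. Section 2.3 says "The physician, patients, assessors, and analysts will all be blinded to the allocation" and describes a placebo matched in package, appearance and taste. Section 2.5 adds a post-treatment period: "The patients will be followed for another 4 weeks after the treatment".

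**The concern.** In a placebo-controlled trial, the comparison of the randomised arms shows whether the test product causes an event. A judgement on a single patient, made blind and in a population on several medicines, is a weak substitute. Under the wording of section 2.5 that judgement comes first and decides what the comparison can see.

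The population makes this matter. The Introduction lists hypertension, heart failure, bone disease, anemia and gastrointestinal symptoms as risks from stage 3 onward. A harm that resembles one of these is easily put down to the disease, and an unexpected harm is easily called unrelated. Under this rule neither would be recorded as an adverse event, and an event never recorded may not be recoverable later.

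At stake is the safety half of the stated aim: incidence would be understated, and a real excess in the treatment arm would be harder to see.

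**Working it through.** **1. The plan's own figure.** The restriction rests on no number. The sample size is checked only because it sets the size of the safety comparison.

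- Inputs (section 2.6): changes of 7.21 ± 4.36 and 4.35 ± 3.15, two-sided α 0.05, β 0.2, dropout 20%, total 72. Section 2.3 gives 1:1 allocation.
- Difference: 7.21 − 4.35 = 2.86. Pooled SD: √((4.36² + 3.15²)/2) = 3.80.
- Normal approximation: n = 2(1.96 + 0.84)² × 3.80² / 2.86², which rounds up to 28 per arm; 56 in total; 56/0.8 = 70.
- Exact t test: 29 per arm; 58 in total; 58/0.8 = 72.5.

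Both are within 2 patients of the stated 72, so the figure reproduces. The adverse-event rule does not affect it. The safety comparison has 72/2 = 36 randomised patients per arm.

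**2. What is and is not filtered (section 2.5).**

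| Data | Causality filter? | Timing stated |
|---|---|---|
| Adverse events | Yes, *related* only | None specific |
| Vital signs, physical examinations | No | None specific |
| Fatigue, anorexia, halitosis, nausea, itching, edema scores | No | Weeks 0, 4, 8 |
| Serum creatinine, cystatin C, eGFR | No | Weeks 0, 8 |

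The last three rows would show some harms by arm without any attribution. They do not cover an event outside those measures, and no symptom or renal measurement is stated for the 4 weeks after treatment.

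**3. What a blinded filter does to the comparison.** The article gives no event rates and no attribution shares, so all values here are assumptions. Let p be the true incidence in an arm and q the share of its events judged related; the recorded incidence is p × q. Power for 36 per arm, two-sided 0.05, uses

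Φ[(|p₁ − p₂| − 1.96√(2p̄(1 − p̄)/36)) / √((p₁(1 − p₁) + p₂(1 − p₂))/36)],

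with recorded rates in place of p₁ and p₂, and p̄ their mean.

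| True rates (BC vs control) | Share attributed | Recorded rates | Risk difference | Risk ratio | Power |
|---|---|---|---|---|---|
| 40% vs 20% | 100% both (no filter) | 40% vs 20% | 20 points | 2.0 | 46% |
| 40% vs 20% | 50% both | 20% vs 10% | 10 points | 2.0 | 22% |
| 40% vs 20% | 30% both | 12% vs 6% | 6 points | 2.0 | 14% |
| 20% vs 20% | 50% both | 10% vs 10% | 0 | 1.0 | – |
| 20% vs 20% | 60% vs 40% | 12% vs 8% | 4 points | 1.5 | – |

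The middle row in numbers: 0.40 × 0.50 = 0.20 and 0.20 × 0.50 = 0.10. Of 36 patients per arm, about 14 and 7 with events become about 7 and 4 on record.

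With equal attribution in the two arms, the risk ratio is unchanged and no false difference appears, but the absolute difference and the power shrink. Only the last row, where attribution differs by arm, produces a difference from equal true rates.

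**The case against.** **The arms cannot be compared without bias.** A reader might infer this, but the document does not support it. Section 2.3 blinds physician, patients, assessors and analysts and supplies a matched placebo. A judgement made blind filters both arms alike unless blinding fails or the kind of event gives the arm away, and nothing in the text suggests either. Related events are also kept in the control arm, so its information is reduced but not discarded. This objection stands and limits the point to lost events and lost sensitivity.

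**All safety data are limited to related events.** This is also tempting and also wrong. The sentence that restricts adverse events lists vital signs and physical examinations without restriction, and renal function and symptom scores are collected on every patient.

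**The investigator decides.** The article names no assessor, so that would be inference. Relatedness in the causal sense is the natural reading, but the article does not define the term.

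**It is a condensed article.** Event definitions, collection windows and causality procedures are commonly left to the full protocol, which may well collect every event. This has force against saying that unrelated events will certainly be absent from the database. It does not remove the point, because the article does not leave the matter open: it states a restriction, twice, in the same word. If the full protocol collects all events, the published text misstates it.

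**The sample is small anyway.** With no events among 36 patients, the one-sided 95% upper bound is 1 − 0.05^(1/36) = 8.0%. That limit reflects the sample size and would be numerically the same under all-event recording, so it does not measure this defect.

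**Conclusion.** The point holds as a criticism of the stated recording rule. Adverse events are restricted to related ones in both places that describe them, while safety is a stated aim. A causality judgement by an unnamed assessor therefore decides which adverse events enter the data.

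Under effective blinding the consequence is missed events, understated incidence and a diluted absolute difference. The unfiltered measurements in section 2.5 partly offset it. Between-arm bias would need failed blinding or revealing event types, and is a possibility, not a finding.

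The size cannot be taken from the document. For assumed true rates of 40% and 20%, attributing 50% of events in each arm halves the risk difference from 20 to 10 points, and attributing 30% cuts it to 6 points. The illustration assumes the same attribution share in both arms and all 36 randomised patients per arm. The primary outcome, the efficacy analysis and the total of 72 are untouched. The change should be made, but the design does not turn on it.

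**What to change.** In section 2.5 and in the Methods part of the abstract, replace the reference to related adverse events with all adverse events from first dose to the end of the 4-week follow-up, regardless of causality.

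Record relatedness and seriousness as attributes of each event, with relatedness judged blind to allocation, and name the role that makes the judgement. State that all adverse events are compared by arm first, with related events shown as a subset. If the full protocol already works this way, bring the published wording into line with it.

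The cost is a wording change and slightly more data entry for 72 patients. The sample size does not change.
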